A peer, who has experiential knowledge and similar characteristics as the target population, can cultivate social connections through sharing of realized knowledge. Peer-led training is feasible to administer and effectively improves wheelchair skills, self-efficacy, and satisfaction with participation. Providing *eHealth* training at home fosters autonomy (i.e., choice and volition), while peers enhance feelings of competence (i.e., self-efficacy) and relatedness (i.e., feeling connected). When these three needs are satisfied, autonomous motivation (i.e., engaging in an activity by choice) increases, driving behaviour change and maintenance, such as wheelchair use and social participation. Every province and territory in Canada has implemented delivery of *eHealth*, providing potential partnership opportunities for TEAM Wheels. By integrating a peer-led approach with the *eHealth* training program, we are leveraging two novel strategies. This is a contemporary approach to community rehabilitation with MWC users that builds on innovations we have already developed in Canada. The results of this trial will provide evidence to move forward with implementation of service at the regional health care delivery level. Furthermore, access to TEAM Wheels has the potential for future exploration in the context of rural and remote service delivery, where consumers have even greater restriction to health care access.

**Purpose.** Our purpose is to *evaluate the effect* of a 1-month, peer-led *eHealth* training program (TEAM Wheels) on satisfaction with activity participation and related rehabilitation outcomes among individuals transitioning to MWC use, compared with current wheelchair training practice.

**Hypotheses:** We hypothesize that at post-treatment, the primary outcome of wheelchair-related participation will be significantly higher in the TEAM Wheels group and that post-treatment improvements will be retained at 6-month follow up. We also hypothesize that the TEAM Wheels program will demonstrate clinically and statistically significant differences at post-treatment and at 6-month follow up on secondary outcome measures of wheelchair-specific self-efficacy; skill capacity and performance; health-related quality of life; and objective measurement of mobility.

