**Objectives:****Primary Objectives: Participation**

1. To measure the effect of TEAM Wheels on *satisfaction with participation* in important activities of life compared to current practice;
2. To measure retention of participation benefits at 6-months post treatment.

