**Outcome measures.** At baseline, descriptive characteristics including age, sex, gender, marital status, highest level of education, primary diagnosis related to MWC use, and length of time using the MWC will be collected. Five outcome measures (available in both French and English) will be administered at baseline, post-treatment, and (for treatment group participants) at 6-month follow-up. The RA will complete the questionnaires with the participant via telephone or Zoom/MS Teams teleconference. The participant will be provided with the questionnaire in advance, via post or email. The RA will collect the data by telephone or teleconference and (subsequently) enter it into a password protected Excel file in the MS Teams database.

*Satisfaction with Participation (primary outcome).* The International Classification of Functioning, Disability and Health (ICF) identifies participation as “involvement in a life situation,” including the subjective experience and performance of important activities and roles. The Wheelchair Outcome Measure (WhOM) is a patient-oriented measure of satisfaction with participation, specifically related to relevant activities inside and outside of the home. The WhOM

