uses user-specific activities, addressing potential sex and gender differences in viewing participation. Two published literature reviews identify the WhOM as the most client-centred and psychometrically robust tool among participation outcomes for wheelchair users. The WhOM is administered as a semi-structured interview. Respondents identify 10 activities (5 performed inside and 5 performed outside of the home), rating their satisfaction with performance on an 11-point scale (0-10) for each activity. The RA will complete the WhOM with the participant via telephone or Zoom/MS Teams teleconference. The participant will be provided with the WhOM form along with the other questionnaires in advance, via post or email. The RA will collect the data by telephone or teleconference and (subsequently) enter it into the MS Teams database. The WhOM demonstrates good reliability (Test-retest ICC = 0.83-0.88; Inter-rater ICC = 0.90-0.91) and validity (correlations with LIFE-H:  $r_s = 0.3-0.5$ ) in use among individuals with spinal cord injury and older adults (Test-retest ICC = 0.77–1.00; correlation with QUEST  $r_s = 0.36 - 0.45$ ). (Auger et al., 2010) A change of 1.6 points has been identified as clinically meaningful. Combined results from our feasibility studies found a large effect size ( $d = 0.93$ ; 95%CI 0.54, 1.33), with mean improvement of 2.3 points. WhOM activities identified by participants (but not the scores) will be shared with their peer trainer to facilitate tailoring of the TEAM Wheels program.

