will be assessed with Maximum Likelihood methods. Data will initially be disaggregated by sex and gender; if analyses prove non-significant, the data will be reaggregated. A repeated-measures ANOVA will be used to evaluate retention of outcomes at follow-up for treatment group participants. Additional post-hoc sub-analyses will investigate the impact of site (using 2-way ANOVA) and length of MWC use covariate (using ANCOVA), although the study is powered only for the primary analysis. Descriptive data will report on recruitment by sex, relative to prevalence data for MWC use to inform generalizability of findings and health services equity balance.

**Sample Size.** The combined results of our feasibility studies found a large effect size ( $f = 0.47$ ) for the WhOM and correlation between measures ( $R^2$ ) was 0.63. Using a comparable effect size ( $f = 0.45$ ) and measure correlation (0.6),  $\alpha = 0.05$ , and 90% power for a between-factors ANOVA repeated measures design, a sample size of 42 is required (G\*Power v.3.1.9.2). Adjusting for 20% loss to attrition, a total sample size of 54 was determined (i.e. 27 per group; intervention and control). We anticipate recruiting 1-2 participants/per site/per month, estimating 12 months required to recruit the sample. Incorporating the treatment and 6-month follow-up periods, the maximum data collection period should be 19 months. While we have built in a 20% attrition rate, our feasibility studies reported 5-10% drop-out rates, (Best et al., 2017; Giesbrecht & Miller, 2017) and with the provision of the TEAM Wheels program to control group participants after data collection, we anticipate little attrition.

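### Retention at 6 months is a primary objective, but the only analysis named for it is a test of difference, with no contrast and no limit on acceptable loss

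*Protocol*

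**What the plan says.** Under Primary Objectives, the second item is "To measure retention of participation benefits at 6-months post treatment". The Hypotheses paragraph expects that "post-treatment improvements will be retained at 6-month follow up". Under Outcome measures, the instruments "will be administered at baseline, post-treatment, and (for treatment group participants) at 6-month follow-up", so the treated arm has three visits. The Assessments section places the last two at weeks 7 and 31. Controls cross over to the programme after week 7, and Methods explains why they have no 6-month visit.

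The Data Analysis section then gives a single sentence on how retention is assessed: "A repeated-measures ANOVA will be used to evaluate retention of outcomes at follow-up for treatment group participants". It does not say which visits enter, which effect or contrast is read, or how much loss would still count as retained. The same section says the study is powered only for its primary analysis.

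**The concern.** The hypothesis is that nothing important is lost between week 7 and week 31. A significance test can reject equality of means but cannot establish it, so the named method points the wrong way for this objective.

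There are two natural ways to use it, and each can mislead:

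- **Overall time effect across three visits.** The baseline to week 7 gain can make this significant by itself. Significance then says that something changed, not that the gain lasted.
- **Week 7 versus week 31 only.** A non-significant result might be reported as retention. With a little over 20 people that is weak evidence, and it becomes easier to obtain as completers fall.

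At stake is a primary objective reported as met when a substantial part of the benefit has gone. With no control group at 6 months, this within-arm analysis is the only evidence on the question.

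**Working it through.** **Inputs**

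- Gain g = 2.3 points, from the feasibility studies ("with mean improvement of 2.3 points", Outcome measures).
- Standardised effect d = 0.93 ("95%CI 0.54, 1.33", same place). The protocol states no SD. I assume SD = 2.3/0.93 = 2.47.
- Correlation between measures 0.6, f = 0.45, alpha 0.05, 90% power, 42 evaluable, 54 in total, 27 per arm (Sample Size).
- Treated completers: 27 with no loss. With the planned 20% loss, 0.8 × 27 = 21.6, taken as 22.
- Meaningful change on the primary scale: "A change of 1.6 points has been identified as clinically meaningful".
- Compound symmetry (equal variances and equal correlations across visits) is assumed throughout.

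**The protocol's own figure.** For the between-group effect, λ = f²·N·m/(1 + (m − 1)ρ), with 1 and N − 2 degrees of freedom. With m = 3 and N = 42, λ = 0.2025 × 42 × 3/2.2 = 11.60 and power is 91.4%. With m = 2, power at 42 is 88.9% and 44 are needed. Attrition gives 42/0.8 = 52.5, so 53 against the stated 54. The sample size reproduces closely. It concerns the comparison between arms, and no figure is given for retention.

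**Overall time effect, three visits, one arm.** λ = n·Σ(μⱼ − μ̄)²/[SD²(1 − ρ)], with 2 and 2(n − 1) degrees of freedom.

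- Fully kept (0, g, g): Σ = g²(4 + 1 + 1)/9 = 2g²/3.
- Fully lost (0, g, 0): Σ = g²(1 + 4 + 1)/9 = 2g²/3, the same value.
- Half lost (0, g, g/2): Σ = g²/2.

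For n = 22, kept or lost: λ = 22 × 3.527/(6.116 × 0.4) = 31.7, power 99.9%. Half lost: λ = 23.8, power 99.2%. The equality of kept and lost holds for any gain, SD, correlation and n, but the level of power does not:

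| Kept = lost, n = 22 | Power |
|---|---|
| g = 2.3, ρ = 0.6 | 99.9% |
| g = 2.3, ρ = 0.4 | 98% |
| g = 1.6, ρ = 0.6 | 93% |
| d = 0.54 (lower confidence limit), ρ = 0.6 | 81% |

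**Week 7 versus week 31 contrast.** The SD of the difference is 2.47 × √(2 × 0.4) = 2.21. At n = 22 the standard error is 2.21/√22 = 0.472. Power comes from the noncentral t.

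| True loss | Significant, n = 22 | Significant, n = 27 |
|---|---|---|
| None | 5% | 5% |
| Half (1.15 points) | 64% | 74% |
| All (2.3 points) | 99.6% | 99.9% |

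So a half loss is non-significant, and could be called retained, in 36% of trials at n = 22 and 26% at n = 27. At n = 18 it is 45%.

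**Confidence interval against a loss limit.** At n = 22 the 95% half-width is 2.08 × 0.472 = 0.98 points. If nothing is lost, the chance that the interval excludes a loss as large as the limit is:

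- limit 1.6 points: 1.6/0.472 = 3.39 standard errors, 90%;
- limit 1.15 points: 1.15/0.472 = 2.44 standard errors, 64%.

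If the true loss equals the limit, the chance of wrongly concluding retention is 2.5%. The success chances depend on the correlation. At ρ = 0.4 the standard error is 2.47 × √1.2/√22 = 0.578, and they fall to about 75% and 48%.

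**The case against.** A reader might infer that the planned ANOVA is significant in over 99% of trials whatever happens, and therefore cannot answer the objective. The protocol does not support that. It never names the overall F test, or a p-value on either side of 0.05, as the criterion for retention. A repeated-measures model also yields visit contrasts. The week 7 versus week 31 contrast is significant in about 5% of trials when the gain is kept and in over 99% when it is lost, so the named method can separate the extremes. The 99% level also rests on an SD the protocol does not give, and it falls under less favourable inputs.

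Two further points are fair. The choice of visits and contrasts is often left to a statistical analysis plan, which is not at hand. And 22 completers is the cautious end: the protocol cites 5–10% drop-out in its feasibility studies and expects little loss.

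All of this stands, and it limits the claim. What remains is that the protocol fixes a method for a primary objective, and no significance reading of that method supports a hypothesis of no loss. Adding contrasts would not cure this without a stated acceptable loss. Full enrolment lowers the missed half-loss rate only to 26%.

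**Conclusion.** The point holds as a mismatch between a primary objective and its named analysis. It does not show that the data cannot answer the question. That the overall time effect cannot tell a kept gain from a lost one follows from algebra under compound symmetry. The specific percentages are conditional on the 2.3-point gain, the derived SD and the correlation of 0.6. The weakness of the pairwise reading is not total insensitivity: it concerns partial losses, where a non-significant result is common. Severity is moderate, because the between-group comparison after treatment is untouched and the repair needs no change to design or data collection.

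**What to change.** Amend the retention sentence in Data Analysis, and carry the change into the analysis plan, as follows:

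- Make the treated-arm mean change from week 7 to week 31, with its 95% confidence interval, the retention analysis. It can come from the same repeated-measures model.
- State that neither a significant overall time effect nor a non-significant week 7 versus week 31 contrast will be read as retention.
- Conclude retention only if the interval excludes a loss larger than a limit that the investigators fix and justify before any 6-month data are examined.
- Report the baseline to week 31 change alongside, so that a small loss is seen against the size of the gain.

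The limit is a judgement for the investigators. The protocol's 1.6-point meaningful change is one candidate, but it is 1.6/2.3 = 70% of the expected gain, which many would find generous. Half the gain (1.15 points) is stricter and has a lower chance of success, about 64% against 90% at n = 22.

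The cost is one paragraph of text. The downside is that retention becomes harder to claim, and with a strict limit the trial may end without a firm conclusion on it even if nothing is lost.

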## Methods:

**Research Design.** This RCT employs 3 sites (Vancouver, Winnipeg, Quebec City) comparing a 4-week MWC training intervention and wait-list control group among individuals transitioning to MWC use. TEAM Wheels will be delivered in the community specifically targeting new users, defined in the literature as individuals within one year of receiving their MWC.

**Methods.** Participants will be randomly assigned to the TEAM Wheels or control group using a 1:1 allocation ratio between groups. To support balance between groups and masking of assignment, our statistician ([name]. – Quebec City) will create a computerized randomization process with undisclosed block size. Randomization will be stratified by site to ensure comparable treatment group size ( $n \sim 18$  per site). Given the potential benefits of the intervention already reported in our previous studies, control group participants will also receive the TEAM Wheels intervention following a 4-week control period and post-treatment data collection (they will be on a “wait-list” for the TEAM Wheels program and receive **no intervention** during the study period).

Following enrolment, baseline data will be collected and entered into a secure MS Teams database. MS Teams data storage is approved by the University of Manitoba Health Research Ethics Board (HREB) and is *Personal Health Information Act* (PHIA)/*Freedom of Information and Protection of Privacy Act* (FIPPA) compliant. The site Research Assistant (RA) will then obtain the participant’s group assignment and coordinate timing for the first teleconference peer trainer session conducted via the computer tablet; for treatment group assignments this will occur as soon as is practical and for control group assignments this will be scheduled after blinded post-treatment data collection is complete. The Research Assistant will also arrange blinded follow-up (retention) data collection for treatment group participants 6 months after post-treatment data collection. Although collecting 6-month retention data for the control group would be optimal, delaying a potentially beneficial intervention and the associated risk of participant attrition make this option undesirable.

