***eHealth* Home Training Program: Mounting system for in-chair use and software**

The tablet displays feedback to the participant on training activity and weekly progress relative to these targets. The tablet software incorporates over 200 video-based training elements including instruction, peer demonstration, and practice activities and games. The tablet software records all home training activity and uploads this data to a secure server. For participants without Internet access, a portable Wi-Fi hotspot device is provided. The peer trainer monitors participant progress online and may adapt the program, or follow-up with the participant, based on their progress data. Participants and peer trainers can also exchange messages when necessary, using the *eHealth* tablet (participant) and The Zoom/MS Teams platforms or email.

**Control Group.** The control group receives no specific intervention over the course of the 4-week period; this reflects “usual practice” or the typical experience of a MWC user in their provincial context. Participants are placed on a wait-list and receive the TEAM Wheels program, as described, following completion of the study (i.e. after post-treatment data collection from the Intervention group). The site Research Assistant will make contact with control group participants at the end of weeks 2 and 4 during the study period to deter attrition/drop-out. When contact is made at week 4, the Research Assistant will schedule an appointment for post-treatment data collection (week 7). Any formal MWC training received during the wait-list period will be documented for potential post-hoc analysis as a confounding variable; however, research evidence and the investigators’ clinical experience confirm that in all 3 provinces formal training is not provided once MWC users are discharged from hospital.

**Data Analysis.** After testing for assumptions and outliers, between-groups (intervention vs control) comparison of change over time will be conducted using Generalized Linear Modeling (GLM) for participation; MWC skill capacity and performance; self-efficacy; health-related quality of life; and objective MWC mobility parameters ( $\alpha = 0.05$ ). Variables previously identified in the literature as relevant covariates (i.e. age and function as measured by baseline WST-C) will be controlled for. Model fit ( $R^2$ ), regression coefficients ( $CI_{95\%}$ ), and effect sizes ( $F^2$ )

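### The 90% power at N=42 is computed for a group main effect averaged over time, not for the between-group difference in change that the protocol plans to test

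*Protocol*

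**What the plan says.** The protocol's Sample Size paragraph takes an effect of f = 0.47 from the combined feasibility studies and reports that the "correlation between measures ( $R^2$ ) was 0.63". It then enters f = 0.45, a "measure correlation (0.6") and alpha 0.05 into G*Power and concludes: "90% power for a between-factors ANOVA repeated measures design, a sample size of 42 is required". Allowing for 20% attrition, the total becomes 54, or 27 per group.

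The Data Analysis paragraph describes a different test. The between-groups "comparison of change over time will be conducted using Generalized Linear Modeling (GLM"), adjusted for age and baseline WST-C. The Hypotheses paragraph places the primary difference at post-treatment. The Data Analysis paragraph also says that the study is powered for the primary analysis only.

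Controls are measured at baseline and post-treatment. Six-month data come from the treatment group alone; the Methods section concedes the point: "Although collecting 6-month retention data for the control group would be optimal", but rules it out. The only repeated-measures ANOVA in the plan is for retention within the treatment group, so it has no group factor.

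**The concern.** A between-factors repeated-measures test compares group means averaged over all measurement times. Baseline is collected before the group assignment is obtained, so its expected group difference is zero, and averaging it in halves a post-treatment difference. A comparison of change subtracts baseline instead. The two tests differ in the effect they target, in their variance and in how they respond to correlation: a higher r lowers power for the averaged contrast and raises it for the change contrast. Nowhere does the protocol plan to test the averaged contrast.

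What is at stake is the protocol's only justification for its sample size. As written, a reader cannot tell what power the primary analysis has, because the test, the scale of f and the meaning of the correlation are each either mismatched or undefined.

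**Working it through.** **Inputs.** From Sample Size: f = 0.45, correlation 0.6, alpha 0.05, 90% power, N = 42, 20% attrition, 54 enrolled. From Methods: 1:1 allocation. From Outcome measures: two measurements in both groups, and a feasibility d = 0.93. Half of 0.93 is 0.465, which agrees with the stated f = 0.47, so f = 0.45 is first read as d = 0.9. Power comes from the noncentral F distribution with 1 and N − 2 df unless noted.

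**1. Reproduce the stated figure.** For a between-factors test with m measurements, λ = N f² m / (1 + (m − 1)ρ).
- m = 2, N = 42: λ = 42 × 0.2025 × 2 / 1.6 = 10.63, power 88.9%. N = 44 gives 90.3%.
- m = 3, N = 42: λ = 42 × 0.2025 × 3 / 2.2 = 11.60, power 91.4%. N = 40 gives 89.9%.

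So the stated 42 is reproduced, exactly as the smallest even N with m = 3 and to within about one percentage point with m = 2. The within-between interaction option with the same inputs, λ = N f² m / (1 − ρ), would have given N = 14. The between-factors routine is therefore the one that was used, and the wording is not just a loose label.

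Attrition: 42 / 0.8 = 52.5, so 53, made even at 54. This is consistent.

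**2. Power for the planned contrast, with d = 0.9 on the raw SD.** The variance of a change score, in raw-SD units, is 2(1 − r), so λ = (N/4) d² / [2(1 − r)].
- r = 0.6, N = 42: λ = 10.5 × 0.81 / 0.8 = 10.63, power 88.9%.
- r = 0.6, N = 54: λ = 13.5 × 0.81 / 0.8 = 13.67, power 95.2%.

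**3. Why this agrees with step 1.** Since f² = d²/4, both λ equal N f² times a multiplier: 2/(1 + r) for between-factors with m = 2, and 1/[2(1 − r)] for change. At r = 0.6 these are 2/1.6 and 1/0.8, both 1.25. Away from 0.6 they separate. At r = 0.4 and N = 42 the between-factors routine gives 92.5% and the change contrast 73.8% (λ = 10.5 × 0.81 / 1.2 = 7.09).

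**4. If f = 0.45 is on the SD-of-change (partial) scale.** λ = N f².
- N = 42: λ = 8.51, power 81.2%.
- N = 54: λ = 10.94, power 90.1%.

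**5. If 0.63 really is R-squared.** r = √0.63 = 0.79. On the raw-SD scale at N = 42, λ = 10.5 × 0.81 / (2 × 0.206) ≈ 20.6, power about 99%.

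**6. If baseline WhOM were added as a covariate (not currently planned).** λ = N f² / (1 − r²). With r = 0.6 and N = 42, λ = 8.505 / 0.64 = 13.29, power about 94% (N − 3 or N − 5 df).

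| Planned change contrast, f = 0.45 | 42 completers | 54 completers |
|---|---|---|
| Raw SD, r = 0.6 | 88.9% | 95.2% |
| Raw SD, r = 0.79 | about 99% | above 99% |
| SD of change | 81.2% | 90.1% |

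No gain from adjusting for age and WST-C is included, because the protocol gives no figure for it.

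**The case against.** The best defence is that nothing material follows. On the most direct reading of the inputs, d = 0.9 and r = 0.6, the planned change comparison has 88.9% power at 42, about one point below the claim. Enrolling 54 with 20% loss leaves 43 completers and 89.6%. The arithmetic reproduces and enrolment would not change. That stands, and it limits the finding to the justification rather than the size of the trial. It does not rescue the text: the agreement is an accident of r = 0.6, and the effect scale on which it depends is not stated.

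Three stronger readings are tempting, and the protocol does not support them.
- **That the trial is badly underpowered.** A post-treatment d of 0.9 becomes 0.45 SD when averaged with baseline (f = 0.225), and the named test then has 36% power at 42. But no planned analysis uses that test, so no inference in this trial has 36% power.
- **That the correlation entered is wrong.** The text calls 0.63 a correlation and carries 0.6 forward as one, so a mislabelled r is at least as plausible as a true R-squared. If it is R-squared, the planned contrast gains power.
- **That f is a partial effect.** The separate participation eta-squared values for the two programmes (0.32 and 0.11) make this possible, but nothing links them to the pooled f. It belongs in a range and is not an established fact.

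The number of measurements entered is also not stated; three is only inferred from the match at 42, and the difference from two is small.

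**Conclusion.** The power statement is wrong as written: it describes a group effect averaged over time, while the primary analysis is the between-group difference in change from baseline to post-treatment. The sample size is not shown to be inadequate. For f = 0.45, power of the planned contrast at 42 completers is about 81% if f is scaled by the SD of change, 89% on the raw SD with r = 0.6, and 99% on the raw SD with r = 0.79. Only on the first of these readings does 54 leave no margin for attrition at 90% power. Each figure is conditional on a scale for f and a value of r that the protocol leaves open; the mismatch between the powered test and the planned test does not depend on either.

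**What to change.** Keep 54 and rewrite the Sample Size paragraph for the planned contrast:
- name the test as the between-group difference in change in WhOM from baseline to post-treatment, with two measurements per person;
- state the assumed post-treatment difference in points and its SD, and say whether f = 0.45 is half of a raw-SD d or is scaled by the SD of change;
- give r, not R-squared, and correct or explain the 0.63;
- report about 89% power at 42 completers for d = 0.9 and r = 0.6, or about 81% if f is on the SD-of-change scale.

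Optionally, add baseline WhOM, which is already collected, as a covariate. Under d = 0.9 and r = 0.6 this gives about 94% at 42 completers. The Data Analysis paragraph lists only age and baseline WST-C, so this must be declared as a change to the analysis and not presented as the existing primary model.

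The cost is one rewritten paragraph, plus one line in Data Analysis if the covariate is added. Enrolment and data collection do not change.
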